### Sample size

2.3.

The sample size was estimated using the following formula (46):

$$n\;\left(eachgroup\right)=\frac{\left(p_{0}q_{0}+p_{1}q_{1}\right){\left(z_{1-\alpha /2}+z_{1-\beta }\right)}^{2}}{{\left(p_{1}-p_{0}\right)}^{2}}$$

α is the value of alpha, conventionally 0.05 (two-sided).β is the value of beta, conventionally 0.20.p_0_ is the expected proportion of controls with exposure.p_1_ is the proportion of cases with exposure.q_0_ = (1 – p_0_).q_1_ = (1 – p_1_).

The prevalence of obesity in the Portuguese adult population was reported as being 17.7% in 2019 (47). Strong evidence suggest that circadian misalignment contributes to obesity and that the metabolic disorders’ genetic components underlie the large interindividual variation in body weight. Studies have highlighted that the genetic component can contribute for 40%–70% of obesity cases (48). Considering that the chronotype is related to clock gene expression, we assumed that an average of 55% of individuals with obesity will have a clock gene-mediated genetic contribution to the obesity phenotype. Based on these assumptions:

p_0_ = proportion of controls with obesity = 0.18.p_1_ = proportion of obesity cases with chronotype misalignment = 0.55.q_0_ = (1 – p_0_) = 1–0.18 = 0.82.q_1_ = (1 – p_1_) = 1–0.55 = 0.45.z _(1 – α/2)_ = 1.96 (value of the standard normal distribution corresponding to a significance level of alpha [1.96 for a 2-sided test at the 0.05 level]).z _(1 – β)_ = 0.84 (value of the standard normal distribution corresponding to the desired level of power −80%).

The sample size necessary for this study is of 46 participants (23 cases and 23 controls). Having into consideration an attrition rate of 40% for visits 2 and 3, the minimum sample size estimated is 64 (32 for each group), to prevent and account for the potential high drop-out rate, incomplete data, and consent withdrawal.

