### Statistical analysis

2.6.

Statistical analysis will be performed using the IBM SPSS Statistics software version 28.0.1. (IBM Corp., Warrington, United Kingdom) and GraphPad Prism version 8 (GraphPad Software, Inc.; San Diego, United States). Continuous variables will be presented as the mean ± standard deviation (SD), median, and interquartile range [Q1–Q3]. Categorical variables will be presented in frequency and percentage. The normality of continuous variables will be tested using the Shapiro–Wilk test if *n* < 50 or the Kolmogorov–Smirnov test if *n* ≥ 50. Parametric tests (Independent Sample *t*-test) will be used to compare the differences between the study and the control groups if the data has a normal distribution, otherwise, non-parametric tests (Mann–Whitney *U*-tests) will be performed. According to the normality or non-normality of data distribution, Spearman’s rank-order correlation (ρ) or Pearson’s correlation coefficient (r) will be performed to calculate and assess the strength of correlations between the study variables. Statistical significance will be set at *p* < 0.05.

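### Section 2.6 lets a normality test choose between the t-test and Mann–Whitney and does not address unequal variances, so the 5% level is not assured if both completers and SDs differ between groups (minor)

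*Protocol article*

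**What the plan says.** All of this stands in one paragraph of the protocol article, section 2.6 (Statistical analysis).

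- **Pre-test.** "The normality of continuous variables will be tested using the Shapiro–Wilk test" when n is below 50. From 50 upward the check is the "Kolmogorov–Smirnov test if" n ≥ 50. The text does not say whether n is counted per group or over both groups together.
- **Group comparison.** The Independent Sample t-test "will be used to compare the differences between the study and the control groups if the data has a normal distribution"; otherwise Mann–Whitney U is used. No unequal-variance form, variance check or transformation is mentioned.
- **Correlations.** "According to the normality or non-normality of data distribution", the text offers Spearman's coefficient first and Pearson's second.
- **Level.** "Statistical significance will be set at" p < 0.05. The Sample size section (2.3) makes this two-sided: "α is the value of alpha, conventionally 0.05 (two-sided").

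Section 2.3 plans 32 per group and allows 40% attrition for visits 2 and 3. The Discussion gives 20% drop-out. Neither figure is split by group, and no SD is given for any outcome.

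**The concern.** Choosing each test from the data means that different biomarkers may be judged against different null hypotheses, and nobody can say beforehand which. The more practical issue is variance. Table 1 confines controls to a BMI of 18.5 to under 25, while the obesity group starts at 30 with no upper limit. Variables that follow adiposity may therefore spread more in the obesity group. The equal-variance t-test copes with this when the groups are the same size, but not when they differ. With the attrition the article expects, completers may well differ.

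The correlation sentence matters because section 2.5.4 uses the food diary to correlate intake with circadian biomarkers. Taken in order, the sentence assigns the rank coefficient to normal data and the linear coefficient to non-normal data, which is the reverse of the usual pairing.

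**Working it through.** **1. The plan's own group sizes.** The inputs are in section 2.3: p0 = 0.18, p1 = 0.55, z = 1.96 and 0.84.

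n = (0.18×0.82 + 0.55×0.45) × (1.96 + 0.84)² / (0.55 − 0.18)² = 0.3951 × 7.84 / 0.1369 = 22.63, so 23 per group. This reproduces. The 64 recruited matches 46 × 1.4 = 64.4.

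**2. Plausible completers (assumed splits).** From 32 per group, 40% loss leaves 32 × 0.6 = 19.2 and 20% loss leaves 32 × 0.8 = 25.6. The cases examined are:
- equal groups of 19, 23 or 32;
- 19 vs 26, one stated rate in each group;
- 16 vs 22, i.e. losses of 50% and 30%, averaging 40%;
- 19 vs 32, all loss in one group, which is extreme.

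SD ratios of 1.5 to 3 are also assumptions.

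**3. Why the pooled variance matters.** Take 19 with SD 2 against 32 with SD 1.
- Pooled variance = (18×4 + 31×1)/49 = 2.102.
- Squared standard error used by the test = 2.102 × (1/19 + 1/32) = 0.1763.
- True value = 4/19 + 1/32 = 0.2418.
- The standard error is too small by the factor √(0.1763/0.2418) = 0.854. The critical value 2.010 therefore acts as 1.716.
- On the Welch degrees of freedom (about 23) the two-sided error is about 9.9%.

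With the SDs exchanged, the pooled variance is (31×4 + 18×1)/49 = 2.898. The factor is √(0.2431/0.1776) = 1.170, and the error is about 2.3%. With equal n the factor is exactly 1 whatever the SD ratio.

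**4. Simulation of the whole rule.** Normal data, Shapiro–Wilk in each group, then the equal-variance t-test if both pass and Mann–Whitney otherwise. The 16 vs 22 row and its reverse used 8,000 runs and were not run at ratio 3; the other rows used up to 4,000.

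| Completers (first group has the larger SD) | SD ratio 1.5 | 2 | 3 |
|---|---|---|---|
| 19 vs 26 | 6.8% | 7.7% | 9.3% |
| 16 vs 22 | 6.6% | 7.8% | – |
| 19 vs 32 | 7.6% | 9.9% | 11.3% |
| 26 vs 19 | 4.3% | 3.6% | 3.4% |
| 22 vs 16 | 4.2% | 3.8% | – |
| 32 vs 19 | 3.2% | 2.7% | 1.9% |

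Repeat runs put the most extreme cell (19 vs 32, ratio 3) between 11 and 13%. Equal groups gave 4.7 to 6.1% over SD ratios of 1 to 3. Unequal groups with equal SDs gave 4.8 to 5.1%. Welch's test alone stayed at 4.3 to 5.6% throughout. Testing normality on the pooled sample gave the same pattern (19 vs 32: 7.1%, 8.6%, 9.9%).

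**5. Separating the cause.** With Welch in place of the equal-variance t-test inside the same pre-test rule, error is about 5 to 6%. The pre-test therefore adds at most about a point.

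**6. Power on skewed markers.** Lognormal data, 23 per group, assumed shift of 0.8 log-SD:

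| Log-SD | 0.3 | 0.5 | 0.8 | 1.0 |
|---|---|---|---|---|
| Plan's rule | 74% | 74% | 74% | 72% |
| Welch on logs | 75% | 76% | 75% | 75% |
| Welch on raw values | 73% | 71% | 64% | 56% |

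Across the group sizes tried, the rule is about 1 to 4 points below the log-scale analysis. It is clearly better than Welch on raw values once skewness is strong.

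**The case against.** The strongest reply is that inflation needs three things together: unequal completers, unequal SDs, and the larger SD in the smaller group. The article states none of them. The design is 1:1, attrition is one overall figure, and the reverse arrangement makes the test conservative. All of this stands. A reader might infer that unequal attrition by itself raises false positives. It does not: with equal SDs the rule holds its level.

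Second, the article never says that variances are pooled, and a condensed article may leave the form of the t-test to an analysis plan. That also stands, and it makes the error-rate point conditional. It does not dispose of the matter, because the article does fix a data-driven choice of test.

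Third, the markers most likely to be skewed go mainly to Mann–Whitney, which gives the same result on raw and logged values. A reader might infer a serious loss of power or an analysis on the wrong scale; the figures do not support either. Nor is the weakness of Kolmogorov–Smirnov much of an argument. It applies only if n is counted over both groups and at least 50 remain, whereas 40% loss from 64 leaves about 38.

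Fourth, the correlation sentence has no word that forces an in-order reading. It may be only a slip of drafting, but it should still be corrected.

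**Conclusion.** The concern holds as a minor one. Section 2.6 lets a normality test select the group comparison and says nothing about unequal variances. If the equal-variance t-test is meant, the nominal 5% becomes about 7 to 11% when the smaller group has the larger SD, and about 2 to 4% when the larger group has it. It stays at about 5 to 6% when group sizes are equal. These figures rest on assumed SD ratios of 1.5 to 3 and assumed splits of attrition, since the article gives neither, and on normally distributed data. The pooled variance accounts for nearly all of the departure. The documents do not show that inflation will occur, only that the rule does not guard against it. The correlation sentence is a separate wording error in the same paragraph.

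**What to change.** In section 2.6:

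- Stop using the normality test to select the analysis, and name the test for each variable before the data are seen.
- Use Welch's t-test for group comparisons, with plasma biomarkers log-transformed and gene expression on the ΔCT scale, which section 2.5.2 already uses. Report differences, or ratios after back-transformation, with 95% confidence intervals.
- Do not apply Welch to raw values of strongly skewed markers, since that would lose power against the present rule.
- Keep Mann–Whitney as a sensitivity analysis.
- Reword the correlation sentence so that Pearson goes with normal and Spearman with non-normal data, or use Spearman for skewed variables throughout.

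The cost is a rewrite of one paragraph. No further data are needed, and the power lost by Welch when variances are in fact equal is negligible.

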The conversion of food into energy and nutrients will be based on the Portuguese Food Composition Table (54), incorporated into the app and, if necessary, other food composition tables. In the app’s food diary section, participants can also upload pictures of the nutritional information/food labeling of the food items being consumed, if available. In the backoffice, it is possible to continuously adapt and complete the information on the Portuguese Food Composition Table by adding nutritional information for new food items or meals. The Portuguese Food Frequency Questionnaire (FFQ) is a validated semi-quantitative instrument that assesses dietary intake, reporting the previous 12 months. This tool will be used to collect information on the consumption of less frequently eaten foods and, therefore, minimize interferences with the day-to-day variation of food intake (55). The Portuguese FFQ includes a pre-determined list of 86 food items or groups, and nine frequency categories ranging from “Never or less < 1 per month” to “6+ per day” (56). Food consumption is quantified by multiplying the reported intake frequency by the food item or group average standard portion, and by a seasonal variation factor for items consumed only in a specific season. The conversion to nutrients will be supported by a compilation of databases on the nutritional food composition, including the Portuguese Food Composition Table (54).

The data collected with the FFQ will be mainly used to perform a global characterization of the participants’ dietary intake in the previous 12 months. The data collected using the 3-day food diary will be used to correlate dietary intake and circadian biomarkers.

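### The correlation rule lists its methods in transposed order: read in sequence, normal data get Spearman and non-normal data get Pearson (minor)

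*Protocol article*

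**What the plan says.** Three statements in section 2.6 (Statistical analysis) belong together.

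- **Normality check.** "The normality of continuous variables will be tested using the Shapiro–Wilk test if *n* < 50 or the Kolmogorov–Smirnov test if *n* ≥ 50".
- **Group comparisons.** The t-test is tied to normality: "Parametric tests (Independent Sample *t*-test) will be used to compare the differences between the study and the control groups if the data has a normal". For variables that fail the check, the article turns to ranks: "otherwise, non-parametric tests (Mann–Whitney *U*-tests) will be performed".
- **Correlations.** "According to the normality or non-normality of data distribution, Spearman’s rank-order correlation (ρ) or Pearson’s correlation coefficient (r) will be performed". The stated purpose of this step is "to calculate and assess the strength of correlations between the study variables".

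The significance criterion is common to all of them: "Statistical significance will be set at *p* < 0.05".

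Section 2.5.4 (Dietary intake assessments) names one use of the correlation rule: "The data collected using the 3-day food diary will be used to correlate dietary intake and circadian biomarkers". Section 2.6 offers no other method for an association between two continuous variables.

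**The concern.** The result of the same normality check leads to opposite families of method in two consecutive sentences. For group comparisons, normality leads to the parametric test. For correlations, the order of words makes normality lead to the rank-based coefficient and non-normality to Pearson's r.

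The diet–biomarker correlations depend on this sentence. If an analyst followed it in order, the variables that fail the normality check would be the ones given Pearson's r on the raw scale, where a few large values can dominate the coefficient. The variables that pass would be given ranks, at a small loss. An analyst who does not follow the word order finds no stated pairing at all, so the choice of coefficient is not clearly fixed in advance.

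**Working it through.** **1. The wording, side by side.** No figure in the article depends on this sentence, so the main check is textual.

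| Rule in section 2.6 | Normal data | Non-normal data |
|---|---|---|
| Group comparison | t-test (parametric) | Mann–Whitney (rank) |
| Correlation, read in order | Spearman (rank) | Pearson (parametric) |
| Correlation, consistent with the row above it in the article | Pearson | Spearman |

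The conditions are listed as normality, then non-normality; the methods as Spearman, then Pearson. No other section restates the correlation rule, so nothing settles the pairing the other way.

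**2. Inputs for the size of the effect.** From the documents: two-sided alpha 0.05; 46 evaluable participants ("The sample size necessary for this study is of 46 participants (23 cases and 23 controls"); 64 enrolled. Assumed, because the protocol gives no value: a latent bivariate normal correlation of 0.4, and lognormal variables exp(σZ) with log-SD σ of 0.5, 1.0 or 1.5.

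**3. Background check on the n used.** The section 2.3 formula gives (0.18 × 0.82 + 0.55 × 0.45) × (1.96 + 0.84)² / (0.55 − 0.18)² = 22.63, so 23 per group and 46 in all, as stated. That calculation compares two proportions and is untouched by this point.

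**4. Simulated power at n = 64, latent correlation 0.4.**

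| Distribution | Method under the literal rule | Method under the consistent rule |
|---|---|---|
| Both normal | Spearman, about 89% | Pearson, about 92% |
| Both lognormal, log-SD 0.5 | Pearson, about 85% | Spearman, about 89% |
| One skewed only, log-SD 1.0 | Pearson, about 78% | Spearman, about 89% |
| Both lognormal, log-SD 1.0 | Pearson, about 64% | Spearman, about 87% |
| Both lognormal, log-SD 1.5 | Pearson, about 45% | Spearman, about 89% |

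Spearman's rho does not change under a monotone transformation, so its true power is the same in every row. The spread of 87% to 89% is simulation noise. With 4,000 replicates the standard error of a power near 63% is √(0.63 × 0.37 / 4,000) = 0.0076, or about 0.8 points, and repeat runs differed by up to about two points.

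**5. The same at n = 46 (4,000 replicates).** Both lognormal at log-SD 1.0: Pearson 52%, Spearman 75%, a loss of 23 points under the literal rule. Both normal: Spearman 77%, Pearson 82%, a loss of 5 points.

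**6. Type I error.** With true correlation 0, the rejection rates over n = 46 and 64, normal and lognormal at log-SD 1.0, lay between 0.044 and 0.057 for both coefficients.

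**7. Precision.** At n = 64 and log-SD 1.0 in both variables, the standard deviation of the estimate was 0.164 for Pearson and 0.108 for Spearman. With normal data the two were 0.106 and 0.109. The coefficients estimate different quantities when data are skewed, so this comparison is indicative only.

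**The case against.** **The intent is recoverable.** The sentence does not say respectively, so it does not strictly assign either coefficient, and the sentence before it shows the logic the authors had in mind. A statistician would probably guess the pairing. This stands to the extent that the text looks like a drafting slip. A reader might infer that the investigators have decided to analyse skewed data with Pearson; the article does not support that. What remains is that matching order is the ordinary reading, and on the lenient reading the rule is left unassigned.

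**The large losses need heavy skew.** This stands. At log-SD 0.5 the loss is about 4 points (89 − 85), and the figures for log-SD 1.0 and 1.5 rest on assumptions with no source in the article. Heavy skew is plausible for some plasma markers, such as C-reactive protein and interleukin-6. It is less obvious for meal times. Clock-gene expression is calculated by the ΔCT method (section 2.5.2), and ΔCT is a log-scale quantity. If it is analysed on that scale, the lognormal assumption does not apply to it; the article does not say which scale is used.

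**It is not shown to be the principal analysis.** A reader might call these correlations the study's main analysis. The article names no primary analysis, and its sample size rests on two proportions. What can be said is that this is the only rule it states for associations between continuous variables.

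**Validity is largely intact.** Agreed: the simulated type I error stayed near 5% for both methods.

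**Conclusion.** The sentence is wrong as written, and the severity is minor. The order of the two coefficients is transposed relative to the conditions, it contradicts the neighbouring group-comparison rule, and no other part of the article repairs it. That conclusion rests on the wording alone.

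The consequence of following it literally is lost power and precision, without more false positives. The loss runs from about 3 points for normal data to about 44 points (89 − 45) for very heavy skew in both variables, at n = 64 and an assumed latent correlation of 0.4. The upper end should not be read as the expected loss in this study, because the documents give no distribution or correlation from which an expected loss could be worked out.

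**What to change.** Replace the sentence with a rule that names each pairing: *Pearson's r if both variables are approximately normally distributed, Spearman's rho otherwise.* Exchanging the two coefficient names and adding *respectively* would also remove the contradiction, but the replacement sentence also makes clear that the condition applies to both variables in a pair.

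The cost is one sentence. Data collection, sample size and alpha do not change. Using Spearman for every correlation, or Pearson on log-transformed biomarkers, is a possible simplification; it is optional and not needed for the correction.

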## Discussion

3.

In recent decades, there have been breakthroughs in obesity care and treatment. However, despite these advances, there is a major remaining challenge: improving the understanding of the heterogeneity of obesity. This knowledge is essential to determine the best approaches to screen, assess risk, and select personalized and individualized treatments. The findings of this study will provide a better understanding of obesity phenotypes in regard to their chronotype, dietary intake (including meal time and nutrient intake), and circadian and metabolic biomarkers.

The circadian system regulates metabolism through the secretion of hormones, such as cortisol and melatonin (63). Alterations in melatonin and cortisol rhythms, or their blunted secretion, are important attributes of circadian misalignment (64, 65). Melatonin is a major regulator of circadian rhythm, namely sleep–wake cycles and hormone secretion (66). The levels of this hormone typically rise at night and fall during the day, in synchrony with the body’s circadian rhythm. Studies have shown that melatonin can help regulate glucose homeostasis by improving insulin sensitivity and reducing insulin resistance (67, 68). In addition, melatonin has been shown to improve lipid metabolism by reducing the levels of triglycerides and cholesterol in the blood. It may also play a role in regulating appetite and body weight (68–70). Disruptions to the body’s circadian rhythm can lead to alterations in melatonin secretion patterns which can have negative effects on metabolism and overall health, as disrupted melatonin secretion has been associated with an increased risk of metabolic disorders such as type 2 diabetes and obesity. Cortisol is tightly regulated by the circadian system, showing an anti-phasic pattern of secretion compared to melatonin (71). Disturbances in the normal circadian patterns can promote alterations in cortisol secretion patterns, which might have a deleterious effect on metabolism. Cortisol is a catabolic hormone with several essential functions in the body, including the mobilization of glucose from glycogen, amino acids and fats in response to other hormonal signals (71). Prolonged cortisol release can promote insulin resistance and obesity can promote abnormal cortisol levels (66).

Circadian oscillations of gene expression also regulate whole-body metabolism (72). For example, Gaspar et al. showed that patients with obstructive sleep apnea, which is strongly related to obesity (73, 74), have different patterns of clock gene expression compared with healthy individuals (51), further highlighting the importance of assessing the circadian features in disease.

The importance of determining the circadian rhythm has been extensively reported; although it started more focused on pharmacological studies (40), this relevance has extended to nutrition. From this, the concept of chrononutrition emerged, mostly because peripheral circadian clocks are mainly synchronized by food intake (24, 31). Furthermore, the circadian clock also regulates nutrient challenges, through transcription factors that modulate the expression of genes with regulatory roles in nutrient pathways (37, 75) Therefore, there is the potential to improve metabolic homeostasis by coordinating behavioral changes with the body’s daily rhythm. The identification of genetic patterns and signatures in response to dietary intake may guide the advance of new therapeutic approaches.

Designing dietary interventions that account for the quality, quantity and timing of food intake could be an approach to modulate the circadian rhythm and clock-controlled genes and optimize the synchronization of central and peripheral clocks, with a positive impact on overall metabolism. Therefore, the characterization of circadian and dietary makers is a critical first step to underpin therapeutic strategies and to support the adjustment of chrononutritional approaches for the management of chronic diseases such as obesity. In the present study, caloric intake, macronutrients (proteins, carbohydrates, and lipids), and meal times (time of the first meal of the day, time of last meal of the day and overnight fasting period) will be evaluated, in order to assess the impact of dietary intake (timing and nutrients) on circadian rhythm markers.

The research protocol has the advantage of simultaneously evaluating dietary intake, circadian rhythm biomarkers, and metabolic biomarkers in blood samples, of both individuals with obesity and healthy individuals. Taking into account circadian rhythm dysfunction in obesity, a better understatement of the circadian clock might provide important clues regarding overall metabolism and disease progression, helping to design more fitting treatment approaches. Based on previous studies, we expect to find differences in the expression of circadian clock genes between the two groups, particularly, in the expression of BMAL1, PER2, CRY2, and REV-ERBα (51, 76–79).

To minimize the number of visits by participants to the study center, and to attempt to increase study adherence, the food diary, sleep diary, and physical exercise registry will be filled out through the mobile application NutriClock. Previous studies have shown increased satisfaction and preference for mobile applications for reporting dietary intake, compared with conventional methods (80), which is a particularly important observation supporting the methodology of our study. Also, as the data is collected through the NutriClock mobile application, it is immediately available to the researchers, preventing the participant from having to go to the study center to deliver the forms in paper format. Furthermore, if data is not being inputted into the mobile application, the participants receive notifications with reminders of the importance of the diaries. In the backoffice, the researcher is also able to detect immediately, through a color system, if the participants are not collecting data and can contact them, if necessary. The records inserted by participants are evaluated on a daily basis, and the system assigns one of four color levels to each component completed, such as the food or sleep diary. This evaluation is based on two criteria: the time elapsed since the start of registration and the number of registrations made. If the number of registrations exceeds 75% of the total days, the component is marked with a green tab. If the number is between 50% and 75%, the tab is yellow, while an orange tab indicates a number between 25% and 50%. A red tab is assigned if the number of registrations is less than 25%.

Some limitations of this study should be considered, including a potential low acceptance of the protocol, causing difficulties in recruitment, and a high drop-out rate. Therefore, a percentage of 20% of drop-out was taken into consideration when calculating the sample size. This anticipated difficulty in recruitment and acceptance of the study protocol is mostly related to the multiple sample collections, and the requirement of filling out a 3-day food diary, which could potentially be a burden for some participants. Initially, recruitment will be promoted in the Leiria (Portugal) area but may be extended to other areas of the central region of Portugal if necessary. Recruiting participants only in the Leiria area, although more convenient for logistical reasons, could also be considered a limitation, given that all study participants will represent the same geographical area and, therefore, we must be cautious in interpreting and extrapolating data. In addition, to mitigate drop-out, participants who complete the observational study will have the opportunity to have a nutrition education session with a registered nutritionist. Also, participants will have permanent access to all the data that they will introduce in the mobile application. Another potential limitation is related to social bias in the self-reporting questionnaires, especially, in the food diaries, which could lead to an underestimation of food intake (81, 82). The assessment of clock gene expression only at two-time points during the day also represents a pitfall of the study. The circadian rhythm integrity has been previously evaluated by looking at clock gene expression at four-time points in hospitalized patients, allowing a more robust interpretation of the results (50). This protocol is based on outpatient recruitment and collection of blood samples at two different time points during the day for outpatient volunteers carries a significant risk of increasing attrition of the study. To mitigate the risk of misinterpreting the data on circadian rhythm based on two-time point serum biomarkers and clock gene assessment, the Pittsburgh Sleep Quality Index and the Munich Chronotype Questionnaire were added to the protocol to broaden the information obtained by serological analysis.

In conclusion, this study will characterize and compare circadian rhythm biomarkers of healthy individuals and people with obesity, associating this information with dietary intake. The results of this study might provide new evidence to develop more targeted and personalized interventions for nutritionists, endocrinologists, and other healthcare professionals, for the treatment and prevention of obesity and its associated complications.

